**Methods:**

The study is a bicentric intervention conducted in 3 care centers (Pavia and Milan) and 1 secondary school (Rome), involving approximately 200 participants with ASD aged 3 to 35 years. The study consists of an observational phase (T0) and an intervention phase (T1). At T0, biographical data, clinical characteristics, and dietary patterns of participants are collected. Based on T0 findings and existing nutritional recommendations for individuals with ASD, targeted menus are developed and tested. At T1, the same assessment tools used at T0 will be applied to evaluate intervention effects. Additionally, a nutrition education course for caregivers will be implemented between T0 and T1, with a pre- and postcourse knowledge questionnaire to assess its effectiveness.

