### Data Collection

#### Overview

Details of data collected from both participants and their families throughout the study period are presented in the following subsections and summarized in Table 1. Data regarding sociodemographic information, food habits, and feeding behaviors during mealtime were collected through 20- or 25-minute telephone interviews, conducted by a researcher. Data entry is carried out in parallel with data collection, through the daily entry of anonymized data into a preset database.

**Table 1 table1:** Summary of data collection tools.

Tool	Evaluated aspects	Addressed to	Filled out by	T0	T1
CRF^a^	General information of enrolled participants and their families	Parents or caregivers	Researcher (telephone interview)	✓	
KIDMED^b^ [17] (3-24 years) and MEDQS^c^ [18] (25-35 years)	Food habits and adherence to the Mediterranean diet	Parents or caregivers	Researcher (telephone interview)	✓	
BAMBI^d^ [19] (3-11 years) and STEP^e^ [20] (12-35 years)	Risk of food selectivity	Parents or caregivers	Researcher (telephone interview)	✓	
PDTA^f^ [16]	Quantitative and qualitative food consumption	Enrolled participants	Researchers (in presence)	✓	✓
Nutrition knowledge questionnaire	Nutrition course knowledge	Parents or caregivers	Researcher (telephone interview)	Before and after the course	Before and after the course
Satisfaction questionnaire	Nutrition course satisfaction	Parents or caregivers	Researcher (telephone interview)	After the course	After the course

^a^CRF: case report form.

^b^KIDMED: Mediterranean Diet Quality Index for Children and Adolescents.

^c^MEDQS: New Validated Short Questionnaire for the Evaluation of the Adherence of Mediterranean Diet and Nutrition Sustainability in all adult population groups.

^d^BAMBI: Brief Autism Mealtime Behavior Inventory.

^e^STEP: Screening Tool of Feeding Problems.

^f^PDAT: pictorial dietary assessment tool.

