#### Food Habits

Information regarding the food habits was assessed at T0. Specifically, the Mediterranean Diet Quality Index for Children and Adolescents questionnaire [17] and the New Validated Short Questionnaire for the Evaluation of the Adherence of Mediterranean Diet and Nutrition Sustainability in all adult population groups questionnaire [18] (Multimedia Appendices 2 and 3, respectively) were used to assess adherence to the Mediterranean diet and to get an overview of the consumption of the main food groups (fruits, vegetables, pasta and cereals, legumes, fish, meat, and dairy products).

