#### Feeding Behaviors During Mealtime

Information regarding feeding behaviors during mealtime was assessed at T0. Specifically, Brief Autism Mealtime Behavior Inventory questionnaire [19,20], validated for a population of 3-11 years, and Screening Tool of Feeding Problems questionnaire [21], validated for a population of 12-99 years (Multimedia Appendices 4 and 5, respectively) were used to evaluate dysfunctional meal-related behaviors, including FS of participants with ASD.

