### Outcomes and Statistical Analysis

The main outcome of the study testing the improvement of the meal acceptance is an increased food consumption of the proposed targeted meals. Specifically, food acceptance of targeted menus will be calculated as the average intake of the 12 administered set meals, ranging from 0 to 1, comparing results collected at T0 and at T1. The improved food acceptance associated with targeted menus will be estimated assuming a threshold of acceptance of 0.6, calculated as the percentage of cases showing an average PDAT lower than that value. Since the results of the pilot study were encouraging [6], showing an average PDAT greater than or equal to 0.8 in 50% (n=22) of participants, a threshold of 0.6 is assumed as a precautionary measure due to the variability in standard meal composition.

Multiple correspondence analysis at T0 was used to study the association between specific sensory aspects and food consumption, categorized into 5 levels (1=no consumption to 5=total consumption). The analysis produced a map showing the distances between the categories of the qualitative variables and food consumption levels.

Concerning the subgroup of caregivers attending the nutrition education course, statistical analysis will focus on effectiveness evaluation of the course, measured by the comparison of nutrition knowledge score, the prevalence of FS score, and the adherence to the Mediterranean diet score before and after the education intervention and by the dropout rate at the end of the course.

Since no preliminary information is available on the average consumption and variability of the PDAT, the determination of sample size is made on the expectation of a possible decreased propensity of FS. FS is an attitude found in 80% of the population with ASD, starting as early as childhood [6]. Hence, setting a significant level of α=.05 and a test power of 90%, under the assumption that the rate of FS may decrease to 15 percentage points, namely from p(T0)=80% to p(T1)=65%, 150 participants could be sufficient [22].

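### The data-collection schedule places food selectivity and Mediterranean-diet adherence at T0 only, which contradicts the abstract, the planned before/after comparison and the T1 rate in the sample size

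*Protocol article*

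**What the plan says.** Four parts of the protocol article bear on when FS and diet adherence are measured.

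- **Outcomes and Statistical Analysis** assesses the course by nutrition knowledge, by "the prevalence of FS score, and the adherence to the Mediterranean diet score before and after the education intervention", and by dropout.
- **The same section, sample size:** "the determination of sample size is made on the expectation of a possible decreased propensity of FS". The rates are given as "namely from p(T0)=80% to p(T1)=65%, 150 participants could be sufficient".
- **Data Collection:** on FS, "Information regarding feeding behaviors during mealtime was assessed at T0"; on diet, "Information regarding the food habits was assessed at T0". In Table 1 the FS row ("BAMBI^d^ [19] (3-11 years) and STEP^e^ [20] (12-35 years") and the KIDMED/MEDQS row are ticked under T0 and blank under T1. The PDAT row is ticked under both.
- **Abstract, Methods:** "At T1, the same assessment tools used at T0 will be applied to evaluate intervention effects".

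**The concern.** A before/after comparison needs an after value, and a T1 rate needs a T1 measurement. The part of the document that field staff would work from provides neither for FS nor for diet adherence. The blank T1 cells do not look like a slip. The PDAT row in the same table is filled in for both phases, the Meal Assessment subsection says explicitly that the PDAT is used at both, and Meal Assessment and Menu Adaptation names only the PDAT evaluation as repeated at T1.

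The abstract gives the effectiveness of the course in reducing FS as the secondary goal. Principal Findings expects FS to fall and diet adherence to improve. If the follow-up calls are not made, neither expectation can be confirmed or refuted, and a missed post-course interview cannot be recovered later by any analysis plan.

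**Working it through.** **Step 1. Timing of each measure, place by place.**

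| Measure | Table 1 and its subsection | Abstract | Needed by the analysis section |
|---|---|---|---|
| FS (BAMBI/STEP) | T0 | T0 and T1 | before and after the course; rate at T0 and T1 for sizing |
| Diet adherence (KIDMED/MEDQS) | T0 | T0 and T1 | before and after the course |
| Knowledge questionnaire | before and after the course | before and after the course | before and after the course |
| PDAT | T0 and T1 | T0 and T1 | T0 and T1 (main outcome) |

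The abstract's statement cannot easily be confined to the PDAT, because its description of T0 covers biographical data, clinical characteristics and dietary patterns. The first two rows conflict; the last two agree.

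**Step 2. Course-effectiveness measures with an after value under Table 1.** Four measures are listed: knowledge (yes), FS (no), diet adherence (no), dropout (yes, since attrition is recorded during the course). So 2 of 4 lack an after value.

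**Step 3. Does the sample size really use a T1 FS rate?** Inputs from the analysis section: p0 = 0.80, p1 = 0.65, and "setting a significant level of α=.05 and a test power of 90" percent. Sidedness is not stated. For two independent proportions with pooled variance and no continuity correction:

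n = [z_α √(2p̄(1−p̄)) + z_β √(p0(1−p0) + p1(1−p1))]² / (p0 − p1)²

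- p̄ = (0.80 + 0.65)/2 = 0.725; √(2 × 0.725 × 0.275) = 0.63147
- √(0.16 + 0.2275) = 0.62249
- One-sided: (1.6449 × 0.63147 + 1.2816 × 0.62249)² / 0.15² = (1.0387 + 0.7978)² / 0.0225 = 3.3727 / 0.0225 = 149.9, which rounds up to **150** per group. This reproduces the stated figure.
- Two-sided, the same formula gives 185.
- A paired (McNemar) calculation with T0 and T1 assumed independent has a discordant share of 0.80 × 0.35 + 0.20 × 0.65 = 0.41 and gives 153 one-sided, 188 two-sided.

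Every one of these routes needs p(T1). The choice of an independent-groups formula for a single-arm pre/post design is a separate matter and is not pursued here.

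**Step 4. Can another measure supply p(T1)?** BAMBI/STEP is the only tool that Table 1 describes as assessing FS risk. The share of participants with mean PDAT below 0.6 can be computed at both phases, but the document does not define that share as the FS rate. It says FS was used for sizing because PDAT variability was unknown.

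**The case against.** The strongest reply is that the second measurement is intended. The abstract says so, the before/after comparison implies it, and Principal Findings expects change in both scores. The two subsections are in the past tense about a phase already completed (October to December 2024) and do not exclude a later one. The Results section puts the intervention phase in April to June 2025, so nothing had yet been lost. This stands. A reader might infer from Table 1 that FS and diet adherence are definitely never measured again, so that the comparisons have no evaluable participants and the 15-point fall can never be observed. The documents do not support that reading; it takes one side of a conflict as settled.

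It is also fair to say that the main outcome is PDAT intake, that FS is openly a stand-in for sizing, and that the before/after comparison concerns only families attending a voluntary course in Milan and Pavia. Under Secondary Objectives the aim is feasibility, parents' knowledge and the meal experience at home. All this limits the consequence to secondary, subgroup level for the course, but it does not remove the conflict. Staff who follow Table 1 would not collect what the analysis section needs.

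**Conclusion.** The point holds as an internal contradiction. Table 1 and the Food Habits and Feeding Behaviors During Mealtime subsections cannot be reconciled with the abstract and with Outcomes and Statistical Analysis. Provided Table 1 is what is carried out, two of four course-effectiveness measures have no after value, and no FS instrument yields the T1 rate on which the 150 rests. If the abstract is what is carried out, T1 values exist, but they are taken once the targeted menus are in use, so a change in attending families would mix course and menu effects.

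A reader might go further and infer that the trial's primary analysis is lost. It is not: the PDAT is scheduled at both phases everywhere in the document.

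**What to change.** Amend Table 1 and the two subsections so that BAMBI/STEP and KIDMED/MEDQS join the telephone interview already held with course attenders after the course.

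- **Timing:** preferably before the targeted menus start, so that the course effect stands apart from the menu effect. If done at T1 instead, label the result a course-plus-menu change.
- **Instrument:** use the same one at both times for each participant. Note that BAMBI is then used outside its stated 3-11 year range for anyone who turns 12 in between.
- **Sample size:** repeat BAMBI/STEP at T1 in all participants only if the FS rate is kept as the powered endpoint. Otherwise state that the fall from 80% to 65% is a planning stand-in that will not be tested.
- **If no repeat is made:** delete the FS and diet-adherence before/after comparisons.

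The cost is modest. The full T0 interview, sociodemographic part included, takes 20 to 25 minutes, so the addition is shorter than that. With 74 participants enrolled in Pavia and Milan, an upper bound for attenders is 74 × 25 = 1,850 minutes, about 31 hours. Repeating FS in all of the roughly 200 planned participants would need an added call to non-attending and Rome families; counting everyone at full interview length, the bound is 200 × 25 = 5,000 minutes, about 83 hours.

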## Introduction

### Background

In recent years, the scientific community has placed particular emphasis on investigating and elucidating the feeding-related behaviors of individuals diagnosed with autism spectrum disorder (ASD). Research has highlighted the rituals related to mealtime that are frequently observed among this population [1].

Individuals with ASD commonly present various feeding challenges, including food refusal, limited food intake, and behavioral difficulties during mealtime [2,3], which results in imbalanced food habits [4]. These challenges fall under the umbrella term of food selectivity (FS), a term also referred to in the literature as “picky eating” and “fussy eating” [4]. Specifically, FS is characterized by the rejection of specific types of food, whether familiar or unfamiliar, often refusing more foods than they accept [5]. This selectivity may involve entire food groups, such as fruits and vegetables, or foods that share specific sensory characteristics, including taste, texture, or odor. When FS persists over time, the individual can be classified as “picky eater,” which may impact dietary variety and nutritional intake [5].

Valenzuela-Zamora et al [3] reported a prevalence of 23% to 69% for FS among a sample of 247 children with ASD aged 2-18 years compared with 267 children with neurotypical condition, where the prevalence ranges from 1% to 37%.

Specifically, individuals with ASD and FS tend to gravitate toward foods with soft or semiliquid textures, pale hues, mild flavors, homogeneity of hues within the same dish, and dishes containing ingredients of similar, noncontrasting color tones, while they show reluctance toward foods that are bitter, sour, or spicy. Additionally, they often avoid strong colors, strong odors, and high temperatures, leading to the exclusion of entire food groups [1,6] (eg, canned fish or vegetables such as broccoli and cauliflower). Moreover, individuals with ASD exhibit a notable preference for processed foods high in energy, simple sugars, saturated fats, and salt but deficient in essential minerals and vitamins [1]. Such preferences may contribute to an increased risk of becoming overweight or developing obesity and micronutrient deficiencies [2].

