## Methods

### Study Overview

The AUT-MENU study is a single-arm pre- and postbicentric intervention study (without control). The study is conducted by a multidisciplinary team consisting of researchers from the Laboratory of Dietetics and Clinical Nutrition of the University of Pavia and the Research Centre for Food and Nutrition of Rome.

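### The 150-participant figure matches a one-sided, per-group size for two independent samples, so its inputs do not establish 90% power for this paired single-arm study

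*Protocol article*

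**What the plan says.** The sample size paragraph closes the Outcomes and Statistical Analysis section of the protocol article. It explains that no prior information on PDAT consumption was available, so the calculation rests on FS instead. It takes as its starting point that "FS is an attitude found in 80% of the population with ASD", and goes on by "setting a significant level of α=.05 and a test power of 90" percent. The conclusion is "namely from p(T0)=80% to p(T1)=65%, 150 participants could be sufficient [22". The paragraph names no test and no sidedness, and gives no discordant proportion or within-person correlation.

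Study Overview describes a "single-arm pre- and postbicentric intervention study (without control". Meal Assessment and Menu Adaptation has each enrolled participant assessed at T0 and again at T1 over 12 meals. The Abstract plans about 200 participants. The Results section reports 74 enrolled in Pavia and Milan, with Rome not yet started.

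On the baseline rate, the Background cites a different source, which "reported a prevalence of 23% to 69% for FS among a sample of 247 children with ASD" aged 2 to 18 years.

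**The concern.** The paragraph is a complete justification (α, power, two rates, n), so a reader can check it. The n it reports is the one produced by a formula for two separate groups, whereas the trial compares the same people before and after. In a paired comparison of proportions the two marginal rates do not fix the sample size. The proportion of participants who change status must also be known or assumed.

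At stake is whether the sponsor can rely on 90% power, and whether it can judge if 74, 150 or about 200 participants are enough. A second, smaller matter is that the 80% baseline lies outside the range in the Background and the article does not comment on the difference.

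**Working it through.** **Inputs.** From the sample size paragraph: p(T0)=0.80, p(T1)=0.65, difference d=0.15, α=.05, power 90% (z=1.2816). Sidedness is not stated, so both are shown (z=1.645 or 1.960). The T0-T1 correlation phi is my assumption; the article gives none.

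**Step 1: reproduce 150.** For two independent proportions with pooled variance (mean rate 0.725):

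n per group = [z_α·√(2·0.725·0.275) + 1.2816·√(0.80·0.20 + 0.65·0.35)]² / 0.15²

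- One-sided: (1.0387 + 0.7978)² / 0.0225 = 149.9, so 150 per group.
- Two-sided: (1.2377 + 0.7978)² / 0.0225 = 184.1, so 185 per group. With 150 per group, two-sided power is 83.2%.

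The one-sided arcsine formula also rounds up to 150 per group (149.2).

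**Step 2: the paired design.** With P(FS at both times) = 0.80·0.65 + phi·√(0.16·0.2275), the discordant proportion is ψ = 0.80 + 0.65 − 2·P(both) = 0.41 − 0.3816·phi. The McNemar normal approximation gives

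n pairs = [z_α·√ψ + 1.2816·√(ψ − d²)]² / d²

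power = Φ{(d·√n − z_α·√ψ) / √(ψ − d²)}

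| phi | ψ | pairs for 90%, one-sided / two-sided | power at 150, one-sided / two-sided | two-sided power at 200 | two-sided power at 74 |
|---|---|---|---|---|---|
| 0 | 0.410 | 153 / 188 | 89.6% / 82.5% | 91.8% | 52.3% |
| 0.2 | 0.334 | 124 / 152 | 94.4% / 89.7% | 96.2% | 61.2% |
| 0.5 | 0.219 | 80 / 99 | 99.2% / 98.1% | 99.7% | 80.0% |

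The minimum discordance, ψ=0.15 (phi about 0.68), needs 54 / 66 pairs. Two-sided, 150 pairs reach 90% when ψ is about 0.33 or less, that is, phi of about 0.21 or more.

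**Step 3: the baseline.** The same formula with the 15-point fall kept, 150 pairs, two-sided:

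| T0 to T1 | phi=0 | phi=0.5 |
|---|---|---|
| 80% to 65% | 82.5% | 98.1% |
| 69% to 54% | 75.6% | 96.1% |
| 50% to 35% | 74.3% | 95.6% |
| 23% to 8% | 94.8% | 99.8% |

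The effect of the baseline is not monotone. Power falls as the rates approach the middle of the scale and rises again at the low end, where 23% to 8% needs only 124 pairs two-sided at phi=0.

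**The case against.** The strongest reply is that a numerical match does not identify a method. The text says neither one-sided nor per group, and the reference for the calculation is not available here. A McNemar calculation also lands near 150: 153 one-sided at phi=0, or 150 two-sided at phi=0.21. That stands, so the independent-groups origin is an inference. It does not rescue the sentence, because a paired calculation reaches 150 only with a discordance that the article does not give. Nor is this merely detail left to a fuller document: the article presents its inputs as leading to 150, and for a paired comparison they do not determine it.

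A reader might infer that the trial is underpowered. The documents do not support that. Positive correlation is the natural expectation for the same people measured twice. One-sided, 150 pairs give 89.6% at phi=0 and more as phi rises. At the plan's own rates, about 200 pairs give at least 91.8% two-sided for any phi of 0 or above. The 74 enrolled is an interim count from part of the sites.

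A reader might also infer that the article contradicts its own 80%. The two figures cite different sources. The 23% to 69% covers ages 2 to 18, while the trial enrols ages 3 to 35. They are unreconciled rather than contradictory. Nor does a lower baseline always cost power, as the 23% row shows.

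**Conclusion.** The concern holds in a limited form. The stated inputs do not establish 90% power for this design. For 80% to 65% with 150 pairs, two-sided power runs from 82.5% at phi=0 through 90% at phi=0.21 to 98% at phi=0.5. It may therefore lie below or above the stated value, and the article gives no basis for choosing. These figures rest on the McNemar normal approximation, on assumed values of phi, and on complete T0-T1 pairs. The unreconciled baseline widens the range: at 69% to 54%, 150 pairs give 76% at phi=0 and 96% at phi=0.5. The finding is that a stated power is not tied to the design, not that the sample is too small.

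**What to change.** Replace the sample size sentence with a paired (McNemar) calculation that states the sidedness and the assumed discordant proportion. Report power as a range over plausible T0-T1 correlations for 150, for the planned 200 and for the number actually enrolled.

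Base it on a binary outcome measured at both times. Table 1 ticks BAMBI and STEP at T0 only, although the Abstract speaks of the same tools at T1, so FS on those scales may have no T1 value for the whole sample. An average PDAT below 0.6, the threshold in the Outcomes and Statistical Analysis section, is scheduled at both times. Its T0 proportion can be taken from the Pavia and Milan observation phase, which the Results section places in October to December 2024.

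If the FS rationale is kept, reconcile the 80% with the 23% to 69% in the Background, for example by a sensitivity range across baselines.

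The cost is recalculation and rewording, with no change to conduct. The single figure of 90% may become a range that lies partly below 90%.

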## Results

Due to different timelines depending on the centers and schools involved, participant enrollment and data collection will take place at different times between Pavia, Milan, and Rome. In September 2024, enrollment was held in the Pavia and Milan care centers for a total of 74 participants enrolled. The observation phase took place between October and December 2024 for a total of 4 weeks for each center, while the intervention phase is scheduled between April and June 2025. In Rome, the school in which to carry out the study has been selected, but the enrollment phase has not yet started; activities are expected to be carried out similar to those in Pavia and Milan.

